# Quantitative Electroencephalographic Biomarkers for Repetitive Transcranial Magnetic Stimulation Treatment Response Prediction in Mild Cognitive Impairment: A Pilot Study Protocol for Multi‐Center, Assessor‐Blinded, Open‐Label Clinical Trial

**DOI:** 10.1002/brb3.71017

**Published:** 2025-10-31

## Abstract

**Rationale:**

Over 55 million people worldwide suffer from dementia, with 10 million new cases diagnosed annually. Due to the limited efficacy of drug therapies, alternative approaches like repetitive transcranial magnetic stimulation (rTMS) have gained popularity as a non‐invasive, safe method leveraging neural plasticity and brain connectivity. However, its high cost and time commitment highlight the need for biomarkers to predict treatment response.

**Aims:**

This pilot study aims to identify a quantitative electroencephalography (QEEG) biomarker to predict which mild cognitive impairment patients will respond to rTMS. By targeting responders early, clinicians can make rTMS more cost‐effective and time‐efficient, reducing wasted treatment on non‐responders.

**Design:**

This multi‐center, assessor‐blinded clinical trial will examine QEEG biomarkers as predictors of rTMS treatment responsiveness in 25 patients with mild cognitive impairment (MCI). Adults aged 60 years or older will undergo cognitive assessments using the Montreal Cognitive Assessment (MoCA) or mini‐mental state examination (MMSE) and have an electroencephalography (EEG) recording. Participants will complete 10 rTMS sessions targeting the left DLPFC over 2 weeks, with 2000 pulses per session at 20 Hz. Cognitive tests will be repeated post‐treatment, and participants will be classified as responders or non‐responders based on cognitive changes, then baseline QEEG parameters will be compared between the two groups. The primary endpoint is the proportion of responders at ten sessions after rTMS (score post‐intervention > score pre‐intervention = responder, according to the minimal clinically important difference (MCID) threshold (i.e., an increase of at least 3 points or 10% on the MMSE, or an increase of at least 1 point on the MoCA); score post‐intervention ≤ score pre‐intervention = non‐responder). The secondary endpoints are the differences in baseline QEEG features between responders and non‐responders.

**Outcome:**

By identifying responders prior to treatment, we can optimize resource allocation, minimize the time and cost associated with ineffective treatments, and ultimately improve the quality of care for individuals with MCI.

**Trial Registration:**

IRCT registration number: IRCT20240218061042N1 (version updated September 7, 2024)

AbbreviationsMCIMild cognitive impairmentMMSEMini‐mental state examinationMoCAMontreal Cognitive AssessmentQEEGQuantitative electroencephalographyrTMSRepetitive transcranial magnetic stimulation

Dementia is a pathological condition in which the decline in cognitive functions is greater than that of biological aging. Over 55 million people worldwide suffer from dementia, and the World Health Organization (WHO) estimates that 10 million new cases will be diagnosed annually (Bai et al. 2022; Organization). By 2050, this population is predicted to rise to 131.5 million (Prince et al. 2016). The WHO report from 2019 estimates that dementia costs the global economy 1.3 trillion (Organization 2025).

Cholinergic and glutamatergic medications have poor efficacy as therapies for any type of dementia, indicating the necessity for novel therapeutic and preventive strategies. Mild cognitive impairment (MCI) is a transitional, preclinical, asymptomatic state before dementia (Zhang et al. 2019). According to most studies conducted in this field, treatment interventions for mild cognitive impairment yield better and more successful treatment outcomes than those for the more severe forms of dementia (Rogers et al. 2023; Koch et al. 2020).

By leveraging neural plasticity mechanisms, including long‐term potentiation (LTP) and long‐term depression (LTD), transcranial non‐invasive brain stimulation has demonstrated efficacy in producing temporary changes in cognition, emotion, and behavior among individuals with mild to moderate cognitive impairment (Dayan et al. 2013; Moretti and Rodger 2022; Thomson and Sack 2020).

Transcranial magnetic stimulation (TMS) is a non‐invasive brain stimulation technique, a safe method with high tolerability and no major adverse effects such as diabetes, tardive dyskinesia, weight gain, etc. (Lefaucheur et al. 2017; Lefaucheur et al. 2020; Su et al. 2023). Furthermore, cortical excitability, neuroplasticity, and functional connectivity between different brain regions are also altered by repetitive TMS (rTMS) (Wassermann and Zimmermann 2012; Salomons et al. 2014). In TMS, action potentials in neurons can be physically induced by an electromagnetic field or a “pulse” produced by running an electric current through a coil (Barker et al. 1987; Barker et al. 1985). While rTMS has shown promise in improving cognitive function in some individuals with MCI, its efficacy is variable (Yan et al. 2023). Identifying reliable predictors of treatment response would be crucial to optimize treatment selection and improve patient outcomes (Lithgow et al. 2022).

In line with this goal, a 2024 comprehensive meta‐analysis of major depressive disorder research identified frontal theta activity in EEG as the most promising candidate for predicting treatment outcomes (Jin et al. 2024). Building on this finding, ongoing research continues to explore the potential of predictive biomarkers.

Proposed indices of usefulness of magnetic stimulation in major depressive disorder include large spectral power values within the low‐frequency θ2 (6–8 Hz) and α1 (8–9 Hz) sub‐bands in the posterior (parietal‐occipital‐posterior) EEG leads (Iznak et al. 2020), as well as the utilization of artificial neural networks with a sensitivity of 93.33% (Erguzel et al. 2015). Furthermore, it is well‐established that in Alzheimer's disease, the primary component of EEG abnormalities involves alterations in alpha and theta bands (Güntekin et al. 2020). The findings of the 2022 investigation are consistent with this observation, demonstrating that EEG event‐related theta responses may be susceptible to neuromodulation therapies (Kayasandik et al. 2022).

Electroencephalography appears to be the preferred paraclinical tool for identifying potential biomarkers of response to magnetic stimulation treatment due to its non‐invasive nature, high temporal resolution, and relative affordability. Furthermore, quantitative EEG (QEEG) further enhances the analysis of EEG data by providing objective and quantitative measures of brain activity, such as power spectral analysis and brain mapping (Fingelkurts and Fingelkurts 2022). This study is conceived as an exploratory investigation aimed at identifying preliminary QEEG biomarkers associated with treatment response to rTMS in individuals with MCI. Designed as a pilot, this study aims to provide foundational insights into the feasibility and potential direction of QEEG analysis in this context, estimating preliminary effect sizes and characterize signal patterns and identifying potential trends, and generating data to inform the design and sample size calculations of future, more definitive trials. By identifying likely responders prior to treatment, the study aspires to optimize resource allocation, reduce the time and costs associated with ineffective interventions, and ultimately improve the quality of care for individuals with MCI.

## Study Design

1

This pilot, multicenter, assessor‐blinded study recruited adults aged ≥60 years from the Tabari cohort registry. After cognitive screening at Imam Hospital, eligible participants underwent baseline EEG recording. Two weeks later, they received 10 sessions of high‐frequency rTMS (20 Hz) over the left DLPFC at the psychiatrist's clinic. Post‐intervention cognitive testing was performed to classify responders and non‐responders (Fig. 1). The full procedural sequence of the study procedure is described in detail below.

This study design as shown in (Figure 1).

**FIGURE 1 brb371017-fig-0001:**
[figure not shown]
Study design.

### Participants

1.1

#### Setting; Recruitment Method

1.1.1

PERSIAN Organizational Cohort Study (POCS) (Poustchi et al. 2018) is the collaborative participation of medical universities on a population of 200,000 Iranians from all races and ethnicities. The Tabari cohort is a subset of the POCS. The Tabari cohort consists of 4199 adults who voluntarily enrolled in the study. Participants undergo annual follow‐ups conducted by specialists and faculty members from various clinical and basic science departments at Mazandaran University of Medical Sciences. This registry project is conducted free of charge and aims to identify diseases and risk factors. All demographic information of volunteers, including address, telephone number, and medical history, is in this registry (Kheradmand et al. 2019). All participants in the Tabari cohort will be contacted by telephone. After providing a detailed description of the study protocol, adults aged 60 years and older (both women and men) who are registered in the Tabari cohort will be invited to undergo global cognitive screening, provided they are able to attend the visit at Imam Hospital, taking into account any physical or mobility limitations. After completing a demographic checklist (e.g., age range, gender, education level) on the first day of the visit, all individuals without any exclusion criteria undergo a mental state assessment and cognitive tests in line with the cohort group's facilities. However, individuals identified with MCI who are currently eligible to participate in the study according to the study's inclusion and exclusion criteria will be thoroughly informed about the study and legal rights and sign informed consent forms. The next day, after EEG recording, patients who consent to rTMS intervention will then complete a screening questionnaire, supervised by a psychiatrist, prior to the treatment. The participants will all be eligible for TMS operation (Rossi et al. 2009; Mokhtarinejad et al. 2024) based on their responses to a TMS safety screening questionnaire and will then complete an Iranian version of the 28‐item General Health Questionnaire (GHQ) (Ebrahimi et al. 2007).

#### Eligibility Criteria

1.1.2

Inclusion criteria: (1) Persian language. (2) have the ability to visit the hospital. (3) all patients aged 60 years or older. (4) participants will be diagnosed with MCI in the Diagnostic and Statistical Manual of Mental Disorders‐5th edition (DSM‐V) and will be additionally assessed by the Montreal Cognitive Assessment (MoCA) (Badrkhahan et al. 2020) and the Mini‐Mental State Examination (MMSE) (Seyedian et al. 2008; Delbari et al. 2024) “22<MoCA<26 or 20<MMSE<24.” (5) not using of psychiatric or neurological medications. (6) patients who will sign informed consent forms.

Exclusion criteria: (1) a history of severe psychiatric problems such as a major depressive disorder or psychosis. (2) history of any neurostimulation treatments during the past 3 months. (3) contraindications to rTMS intervention, such as the presence of a cardiac pacemaker and ferromagnetic implants in the head or neck. (4) history of serious neurological illnesses, including epilepsy, seizures, or stroke. (5) abusing drugs or alcohol excessively. (6) with a skull fracture or craniotomy.

Patients diagnosed with MCI will be invited for EEG recording the next day. After EEG recording, those who consent to rTMS intervention will complete a screening questionnaire, supervised by a psychiatrist, prior to the treatment. The participants will all be eligible for TMS operation (Rossi et al. 2009; Mokhtarinejad et al. 2024) based on their responses to a TMS safety screening questionnaire. The TMS Safety Screening Questionnaire will be used to evaluate the eligibility for TMS intervention based on the questionnaire from Rossi et al. (2021), covering questions about the existence of risk factors, such as epilepsy or the presence of a cardiac pacemaker and ferromagnetic implants in the head or neck. According to their responses, patients will be categorized as either “Eligible,” or “Not eligible.”

Then complete an Iranian version of the 28‐item General Health Questionnaire (GHQ) (Ebrahimi et al. 2007). The General Health Questionnaire (GHQ‐28) is a general health screening tool, and obtaining a score of 24 (Ebrahimi et al. 2007) or higher is a condition for volunteers to continue participating in the study, as well as not having any TMS contraindications.

#### Informed Consent Process

1.1.3

Informed consent will be received by the investigator involved in this study. Patients will be completely informed in comprehensible terms of the requirements, the risks, the objectives, and safety measures. They will be informed of their right to withdraw at any time without incurring any penalty and to refuse to participate. All of this information is explained in the consent form that will be provided to the participant. The investigator will collect written consent of the participant prior to final inclusion in the study.

### Assessment Tools

1.2

#### Questionnaire

1.2.1

The most popular test for diagnosing dementia is the MMSE, whereas the Montreal Cognitive Assessment (MoCA) is a very accurate test for mild cognitive impairment. To assess volunteers' global cognition, we will use MMSE and MoCA.

Thirty questions make up the MMSE, which evaluates orientation (10 points), immediate recall (3 points), attention and calculation (5 points), recall (3 points), and language (9 points) (Seyedian et al. 2008; Abe et al. 2020).

Eight cognitive domains are evaluated by the thirty questions in the MoCA, which also include executive functions and visuospatial skills (5 points), attention (6 points), naming (3 points), abstract thinking (2 points) language (3 points), recall (5 points), and orientation (6 points) (Badrkhahan et al. 2020). Higher scores on the MMSE and MoCA indicate higher cognitive function; scores range from 0 to 30. Because of the nature of questionnaires, if participants are uneducated (0 year of schooling), we add 3 points to the score of MMSE. Range of the Farsi version of thr MMSE is 20 < MMSE < 24, indicating MCI (Delbari et al. 2024). Besides, in MOCA test, Because the nature of questionnaires, if the subjects have less than 12 years of schooling (1‐11 years of schooling), we add 1 point to the score and range of 22 < MoCA < 26 indicate MCI (Zhao et al. 2011). For educated individuals, we will use MOCA exams. and for uneducated subjects (0 years of schooling), we will only use the MMSE test.

Finally, a history and mental state assessment by a psychiatrist based on the Diagnostic and Statistical Manual of Mental Disorders, fifth edition (DSM‐V), is crucial because the decline or stability of cognitive performance compared to the past is the most important issue (Edition 2013; Kaplan 2015).

MMSE and MoCA tests will be repeated at the end of the treatment to classify participants as responders or non‐responders to the intervention. We will use the minimal clinically important difference (MCID), based on clinically meaningful changes in cognitive test scores. The MCID denotes the smallest change in score perceived as beneficial or significant by patients or clinicians. Detailed thresholds for the MMSE and MoCA tests are comprehensively described in the post‐intervention assessment section.

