#### Questionnaires

1.4.1

After 10 rTMS sessions, we will perform the cognitive tests again under the same conditions. For educated individuals, we will use MoCA exams, and for uneducated subjects (0 years of schooling), we will only use the MMSE test again. If a participant's MMSE or MoCA score increases after the TMS, they will be considered a responder. Conversely, if their score decreases or there are no changes, they will be classified as a non‐responder (Kayasandik et al. 2022).

We will utilize the minimal clinically important difference (MCID) to evaluate significant changes in test scores. According to the MCID, an increase of 3 points or 10% (Borland et al. 2022; Watt et al. 2021) in the MMSE indicates cognitive improvement (Borland et al. 2022; Watt et al. 2021). The MCID for the MoCA may vary, but we will consider a 1‐point increase as a sign of cognitive improvement (Lindvall et al. 2024). After completing the work, patients will receive free visits from the psychosomatic fellowship to continue their treatment in accordance with ethical principles.

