### Group Classification

1.5

MCI with 22 < MoCA < 26 or 20 < MMSE < 24 after 2 weeks of intervention and post‐assessments will be divided into two groups (score post‐intervention > score pre intervention = responder, according to MCID threshold (i.e., an increase of at least 3 points or 10% on the MMSE, or an increase of at least 1 point on the MoCA); score post‐intervention ≤ score pre‐intervention = non‐responder).

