#### Primary Endpoint

1.6.1

The primary endpoint is the proportion of responders according to MCID. Additionally, the primary analysis will determine which cognitive subdomains show the greatest therapeutic effects.

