#### Primary Endpoint

1.7.1

All assessors will be blinded to group allocation and receive data labeled as “group A” and “group B.” Statistical analyses will be conducted using StataNow18.5 (Stata Corp, College Station, TX, USA), adhering to CONSORT guidelines. Normality of continuous variables will be checked using skewness and kurtosis, with variables considered non‐normal if absolute skewness > 2 or kurtosis > 3. Baseline characteristics, including (sex, hyper‐lipidemia, hypothyroid, hyper‐tension, diabetes, smoking, ischemic heart disease, education, and age) will be compared between groups using Fisher's exact test for categorical variables and the Mann–Whitney *U* test for non‐normal continuous variables. For normally distributed continuous variables, between‐group comparisons will be performed using the independent samples t‐test.

Initially, paired *t*‐tests (a suitable transformation or non‐parametric test) or equivalents for non‐normal data will be used to evaluate overall pre‐ to post‐rTMS changes within all 25 participants, assessing global treatment efficacy and identifying cognitive subdomains demonstrating the greatest response. Subsequently, participants will be categorized into responders and non‐responders based on MCID criteria. Between‐group comparisons of cognitive scores and subdomains will then be performed using ANOVA for baseline and ANCOVA for post‐intervention outcomes, adjusting for baseline scores and potential confounders. Pre‐intervention values refer specifically to baseline cognitive test scores, totally and in each cognitive sub‐domain, and related continuous variables measured before rTMS, which serve as covariates in the analyses. The QEEG features are analyzed separately as part of the secondary endpoint assessment. For non‐normal variables, suitable transformation will be applied, and median differences with percentage changes reported. Marginal plots from ANCOVA will visualize adjusted group differences post‐intervention. This two‐stage analytical approach allows comprehensive evaluation of rTMS effects both globally and within clinically meaningful responder groups across cognitive domains.

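### Schooling decides which cognitive test a participant takes, yet MoCA and MMSE results share one responder label, one all-participant analysis and QEEG comparisons with no stated adjustment for test

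*Protocol article*

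**What the plan says.** Section 1.2.1 allocates the instrument by education: "For educated individuals, we will use MOCA exams. and for uneducated subjects (0 years of schooling), we will only use the MMSE test". Section 1.4.1 repeats the split after treatment, where "uneducated subjects (0 years of schooling), we will only use the MMSE test again".

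Section 1.5 defines response by an MCID rule: "an increase of at least 3 points or 10% on the MMSE, or an increase of at least 1 point on the MoCA". The abstract gives the same rule. Section 1.4.1 also gives a simpler one: if the "MMSE or MoCA score increases after the TMS, they will be considered a responder".

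The primary endpoint (1.6.1) is a single proportion of responders. The same section adds that "the primary analysis will determine which cognitive subdomains show the greatest therapeutic effects". Section 1.7.1 tests pre-post "changes within all 25 participants, assessing global treatment efficacy and identifying cognitive subdomains demonstrating the greatest response". Section 1.7.2 compares QEEG features between responders and non-responders by t-test or Mann–Whitney test, followed by ROC analysis. It names no covariate or stratum.

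Education appears once in the statistical methods, among the baseline characteristics compared between groups in 1.7.1. The ANCOVA there adjusts for baseline scores and unnamed potential confounders, but only for cognitive outcomes.

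**The concern.** Test and education coincide by design, because zero years of schooling means MMSE and anything else means MoCA. A responder label that is harder to earn on one test is therefore harder to earn at one level of education. Any EEG feature that varies with schooling could then differ between responders and non-responders without having anything to do with rTMS. Separating responders from non-responders on baseline QEEG is the purpose of the study.

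The pre-post and subdomain analyses have a second problem. As listed in 1.2.1, the tests do not share a subdomain structure. Orientation carries 10 points on the MMSE and 6 on the MoCA, recall 3 and 5, and language 9 and 3. Naming, abstraction and visuospatial/executive function are listed for the MoCA only. No common metric is given, so a mean change or a ranking of subdomains over all 25 participants has no defined unit.

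**Working it through.** The plan gives no expected responder rate, SD or power figure, so there is nothing of its own to reproduce.

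**Step 1: the whole-point thresholds.** Eligibility is "MCI with 22 < MoCA < 26 or 20 < MMSE < 24", that is, MoCA 23–25 or MMSE 21–23. Ten per cent of 21–23 is 2.1–2.3 points, which needs 3 whole points. Ten per cent of the 30-point scale is also 3. The two MMSE criteria therefore agree at +3, against +1 on the MoCA. One reading is softer. For unschooled participants "we add 3 points to the score of MMSE", so raw scores are 18–20, and 10% of those is 1.8–2.0. Then 2 points would be enough, still twice the MoCA rule.

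**Step 2: the same change distribution on both tests.** Assume a normal change with mean m and SD s, rounded to whole points. Then P(rise ≥ t) = 1 − Φ((t − 0.5 − m)/s). The values of m and s are assumptions. With m = 0:

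| Assumed SD | MoCA, P(≥1) | MMSE, P(≥3) | Ratio |
|---|---|---|---|
| 1.5 | 0.369 | 0.048 | 7.7 |
| 2.0 | 0.401 | 0.106 | 3.8 |
| 2.5 | 0.421 | 0.159 | 2.6 |

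With m = 1 and s = 2 the probabilities are 0.599 and 0.227, an odds ratio of 5.1. Over s from 1.5 to 3 and m from 0 to 2, the odds ratio runs from 2.9 to 11.7.

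**Step 3: effect on the primary proportion and the group mix.** Let k of the 25 take the MMSE, with m = 1 and s = 2. Expected responders are (25 − k) × 0.599 + k × 0.227. For k = 8 this is 10.2 + 1.8 = 12.0, or 48%. MMSE takers are 8 × 0.227/12.0 = 15% of responders and 8 × 0.773/13.0 = 48% of non-responders.

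| k on MMSE | Responder proportion | MMSE share of responders | MMSE share of non-responders |
|---|---|---|---|
| 0 | 60% | 0% | 0% |
| 5 | 52% | 9% | 33% |
| 8 | 48% | 15% | 48% |
| 12 | 42% | 26% | 64% |

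The mean change is identical in every row, so only the mix of tests moves the proportion.

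**Step 4: carry-over to QEEG.** Suppose a feature differs by d SD between schooled and unschooled participants and is unrelated to response. The induced responder difference is d times the gap between the last two columns. For k = 8 and d = 0.5 this is 0.5 × (0.476 − 0.151) = 0.16 SD. For d = 0.5–0.8 and k = 5–12 it is 0.12–0.30 SD. The matching AUC, Φ(difference/√2), is 0.53–0.59.

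**Step 5: what the stated adjustments reach.** Comparing education at baseline can reveal an imbalance but does not correct it. The ANCOVA in 1.7.1 covers cognitive scores. Neither touches the responder label, the primary proportion or the analyses in 1.7.2.

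**The case against.** - **The confounding is conditional.** A reader might infer that the label is certainly confounded. The documents do not say how many participants have no schooling, and with none the problem disappears. This stands, and the conclusion is worded accordingly.
- **MCIDs may properly differ between instruments.** This is true, so unequal point thresholds are not in themselves an error. The difficulty is that the instrument follows a participant characteristic and nothing downstream accounts for it.
- **The responder ratios are not a measured effect of the instrument.** A reader might take the 2.6- to 7.7-fold range that way. It rests on zero true change and equal SDs on two different tests, neither of which is in the documents. The direction is robust under equal change distributions; the size is illustrative.
- **The eligibility band shows nothing.** A reader might note that an MMSE responder must score at least 24 and so leave the band. A MoCA participant at 25 leaves it with a 1-point gain too, and the band governs entry, not response.
- **The plan may not mean raw pooling.** Analysing all 25 may simply contrast the whole cohort with the later responder split, and an unseen analysis plan could handle the tests separately. That is possible, but the article fixes one label, one proportion and one all-participant analysis without a common scale.
- **The QEEG bias is modest for a pilot.** With a 12/13 split the standard error is √(1/12 + 1/13) = 0.40 SD, and about 0.12 for the AUC, so the bias in step 4 is below one standard error for a single feature. This tempers the urgency. But the pilot is meant to supply effect sizes for later trials, and a systematic component would be carried into them.

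**Conclusion.** The point holds in conditional form. If unschooled participants enrol, the plan as written ties response to education and test, and leaves the pooled change and the subdomain ranking without a common unit. The MCID thresholds are 1 point against, in practice, 3 (or 2 if the percentage is taken of the unadjusted score). Under the assumptions in step 2 with no true change, 37–42% of MoCA takers and 5–16% of MMSE takers would be called responders. The effect on the primary proportion and the QEEG contrast grows with the unstated number on the MMSE.

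The responder definition also contradicts itself. The any-increase rule in 1.4.1 would set 1 point for both tests and remove the threshold gap, though not the subdomain mismatch. The abstract and 1.5 apply the MCID thresholds but define non-response as a final score no higher than baseline, so an MMSE gain of 1 or 2 points falls in neither group.

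**What to change.** 1. Report the responder proportion and mean change by instrument as well as overall, with the number on each test.
2. Analyse subdomains within each test only, with no pooling across tests.
3. Adjust or stratify the QEEG comparisons and ROC analysis by instrument. If the MMSE stratum is too small, add a MoCA-only sensitivity analysis.
4. Reconcile the any-increase rule in 1.4.1 with the MCID rule in the abstract and 1.5, so that every MMSE change, including gains of 1 and 2 points, is classified.

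All of this uses data already planned. The price is less precision in the by-instrument results, growing with the number on the MMSE: with 12 of 25, a MoCA-only analysis would have 13 participants. Dividing each change by its test's retest SD is less attractive, because one measurement before and one after treatment in a single arm do not supply that SD.
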